### **Long term assessment of FRDA participants taking nicotinamide daily over a two month period, Part III**

If the multiple dose dosing regimen of nicotinamide in Part II is well tolerated and changes in FXN level are observed, all participants (including those who were scheduled to receive no drug in part II) will be offered to enter Part III. Participants who took part in part I but not in part II of the study may also participate. These participants may require re-screening. This decision will be taken by the CI. If required, additional participants will undergo screening and if eligible may enter directly into this part of the study. Participants who took part in Part II will be given the weekly drug supply and diary on Part II Day 5. Participants who took part in Part I but not Part II or participants who will directly enter Part III will be given the weekly drug supply and diary at their screening visit (only once determined eligible) or by courier / recorded delivery post. Their next visit will be Part III, week 1.

Participants who were 'on drug' in Part II will take their MTD already established over the course of two months. If any AEs occur that in the CI's opinion may put the safety of the participant at risk, the dose schedule will be adjusted. If a participant was on 'no drug' in Part II or due to enter Part III directly they will start at a low dose of nicotinamide (typically 2g) which will be gradually escalated in the absence of any AEs which in the CI's opinion may put the participant's safety at risk.

If the participant stops taking nicotinamide for several days (for safety reasons), only once the participants AEs are fully resolved, the CI may decide to add this drug interruption period onto the end of the two month period.

To ensure that sustained FXN upregulation is achieved, the nicotinamide PK/ pharmacodynamic (PD) relationship (i.e. time to nicotinamide steady state vs. upregulation of FXN) will be evaluated at each weekly visit and the daily dose regimen may be modified from once to twice a day [i.e. from 6 grams (or MTD) Once Daily (OD) to 3 grams (or ½ MTD) twice a day (BD)]. In some instances, manufacturing restrictions (i.e. nicotinamide tablets of 500mg) render the division of the dose into two equal doses, for BD dosing, impossible. In these cases patients will receive a slightly different dose in the morning to the evening.

Participants will attend the Imperial CRF prior to taking their dose of nicotinamide once a week ( $7 \pm 2$  days) over this time period. Participants will be provided with study drug supply for  $7 \pm 2$  days and rescue medication (anti-nausea treatment, typically domperidone or metoclopramide). Domperidone or metoclopramide will be taken if required prophylactically [domperidone pre-dose (20 mg oral) and post-dose (20 mg orally up to four times daily)]. Participants will also be provided with their first weekly diary card, which will need to be completed each day for the entire duration of Part III until the interventional end-of-study visit. Participants will record whether or not they took nicotinamide, number of tablets, any AEs and any concomitant medications taken. Each week, the trial diary from the previous visit will be collected and participants will be provided with another diary to complete starting on the next day. Participants and their carers will complete Part II of the Friedreich's Ataxia Rating Scale (FARS): ADL. SARA and SCAFI scales will also be done and a clinician- and/or software-based speech dysarthria assessment will be performed.

### **3) Development of reliable methodologies to measure clinical deficit and subtle neurological changes and correlation of functional changes to levels of expression of FXN protein and the epigenetic structure of the FXN gene (Part IV).**

A minimum of ten up to a maximum of 20 FRDA participants will be offered the opportunity to participate in Part IV. Up to 20 healthy volunteers (HV) will also participate in this part of the study.

Healthy volunteers will have an fMRI assessment during the execution of tasks, perform the SARA and SCAFI and scenarios wearing a body suit, perform eye movement tasks (optional) and perform a balance control task (optional). These assessments do not have to be performed on the same day. Including HV will provide us with a control comparison in individuals without a progressive deterioration.

Participants may be contacted by telephone and/or email or at their study visits (i.e FRDA participants participating in the interventional study) by the CI or delegates to inform them about the potential benefit and any risks associated with participation in this part of the study. fMRI contraindications will be detailed. Participants will be given the PIS and given as much time as they wish to read and ask questions. If the participant wishes to take part, informed consent will be given in writing prior to performing any study-related assessments. Participants will be assessed for fMRI contraindications during screening (including urine pregnancy test for women of child-bearing potential) prior to study start.

FRDA participants will undergo the assessments detailed below over the course of 2 days at the study start, 2 weeks ( $\pm 2$  days), 3 months ( $\pm 2$  weeks) and at 9-12 months ( $\pm 3$  months). In some cases if travel is difficult, participants will be offered overnight accommodation (at the Imperial CRF or private hospital accommodation).

1. Urine pregnancy test only for women of child-bearing potential (prior to fMRI).
2. Blood samples will be taken for:
  - FXN protein estimation by LC-MS/MS compared to the current dipstick assay (Mitosciences);
  - RNA-seq to identify informative biomarkers that might track FXN levels and
  - Analysis of the spatial organisation of the FXN locus by Chromosome-Conformation Capture coupled with high-throughput sequencing (3C-sequencing) to correlate with FXN expression – such a technique may be capable of identifying participants that would be predicted to respond to epigenetic therapies such as nicotinamide.
3. The Edinburgh handedness score will be performed at the study start visit only.
4. Participants will perform standardised tasks derived from the SARA and SCAFI
5. fMRI assessment during the execution of a standardised finger-tapping task (Akhlaghi et al., 2012) and object manipulation. fMRIs will be performed at the Imperial College Centre Imaging Facility (CIF). Participant's hands will be filmed on an fMRI compatible device, which analyses movements in real-time and will be correlated with the fMRI analysis.
6. Participants will be fitted with a simple portable motion-capture device similar to an ECG to be worn overnight. This will be returned the following day.
7. Participants will perform standardised ADL tasks (Appendix 5) and the SARA and SCAFI (not the timed speech test) while wearing a full-body, motion-tracking equipment ('body suit') to capture detailed body kinematics.
8. Chromatin immunoprecipitation studies. Consistent with a recent study (De Biase et al., 2009) we have shown that both H3K27me3 and H3K9me3 spreads on either side of the GAA-repeat when the gene is repressed in participant cells. Samples taken at each visit in part IV will measure the stability of either of these modifications over time and correlate this with clinical phenotype.
9. Participants will perform standardised eye movement tasks to assess the performance of their occulo-motor system quantitatively assessed using a binocular eye-tracking system (optional).
10. Participants will stand on a force plate and their balance performance will be measured (optional).

To enable identification of pathological changes specific to FRDA, identical studies will be performed on healthy volunteers. Healthy volunteers will come over the course of several visits and will perform the following assessments:

1. Urine pregnancy test for women of child-bearing potential only (prior to fMRI).
2. The Edinburgh handedness score.
3. fMRI assessment during the execution of the standardised finger-tapping task (Akhlaghi et al., 2012) and object manipulation. Participant's hands will be filmed on an fMRI compatible device, which analyses movements in real-time and will be correlated with the fMRI analysis.
4. Participants will perform standardised ADL tasks (Appendix 5) and the SARA and SCAFI (not the timed speech test) while wearing a full-body, motion-tracking equipment ('body suit') to capture detailed body kinematics.
5. Participants will perform standardised eye movement tasks to assess the performance of their occulo-motor system quantitatively assessed using a binocular eye-tracking system (optional).
6. Participants will stand on a force plate and their balance performance will be measured (optional).

These assessments can be performed over the course of several days or at different time points.

#### 4.2. Discussion of Study Design

This is an early phase study to ascertain whether upregulation of FXN in participants with FRDA can be achieved with nicotinamide given orally and if so to determine the effective dose. We will determine the safety and tolerability of oral nicotinamide in participants with FRDA when used in a dose range similar to that used in a long-term trial in the prevention of diabetes and in the treatment of participants with radiotherapy. We will also assess the long term clinical effects of FRDA participants taking nicotinamide

daily over a two month period. In addition, the protocol allows for assessment of the downstream effects of FXN on biological pathways using RNA-Seq and the effect on the epigenetic state of the FXN gene following HDAC treatment and a correlation with phenotype to be made.

Part IV will permit us to develop reliable methodology to measure clinical deficit and more subtle change in the neurological state of FRDA participants over a 9-12 month period and will allow us to correlate functional changes to levels of expression of FXN protein and the epigenetic structure of the FXN gene. This part of the study will be conducted without the use of nicotinamide.

Including HV in Part IV will be used to establish a 'normal' baseline. This baseline will provide a way to compare FRDA patients to HVs and enable new clinical scales based on the novel methodology to be established.

#### **4.3. Selection of Study Population**

Participants eligible for the study will be drawn from the FRDA patient population being seen at Hammersmith Hospital, or the National Hospital for Neurology and Neurosurgery (NHNN) or who have contacted us via information posted on ClinicalTrials.gov.

Healthy volunteers will be recruited from the research community or the Imperial CRF health volunteer database. Advertisements will be posted and placed online on the ICRF website.

#### **4.4. Inclusion Criteria for the interventional study**

1. Participants must have a molecular genetic diagnosis of FRDA, consisting of a GAA-repeat expansion on both alleles of the FXN gene.
2. Participants must be over the age of 18 years living in the UK and registered with a GP.
3. Participants must provide informed consent. If written consent is not possible due to physical incapacity, written consent on behalf of the participant will be sought from the participant's relatives or carer.
4. A female participant is eligible to participate if she is of:

Non-childbearing potential defined as pre-menopausal females with a documented tubal ligation or hysterectomy; or postmenopausal defined as 12 months of spontaneous amenorrhea [in questionable cases a blood sample with simultaneous follicle stimulating hormone (FSH) > 40 MIU/ml and estradiol <40 pg/ml (<140 pmol/L) is confirmatory].

Child-bearing potential and agrees to use one of the following contraception methods:

True abstinence: When this is in line with the preferred and usual lifestyle of the participant. [Periodic abstinence (e.g., calendar, ovulation, symptothermal, post-ovulation methods) and withdrawal are not acceptable methods of contraception].

Contraceptive Methods with a Failure Rate of < 1%:

- Oral contraceptive, either combined or progestogen alone;
- Injectable progestogen;
- Implants of levonorgestrel;
- Estrogenic vaginal ring;
- Percutaneous contraceptive patches; -
- Intrauterine device (IUD) or intrauterine system (IUS) that meets the <1% failure rate as stated in the product label;
- Male partner(s) sterilisation (vasectomy with documentation of azoospermia) prior to the female participant's entry into the study;

- Double barrier method: condom and occlusive cap (diaphragm or cervical/vault caps) plus vaginal spermicidal agent (foam/gel/film/cream/suppository).

#### 4.5. Exclusion Criteria for the interventional study

1. Participants with significant clinical dysphagia.
2. Participants taking Sodium Valproate or any other known histone deacetylase inhibitor.
3. Participants taking part in another interventional clinical trial or who have done so within 30 days before screening.
4. Participants known to be positive for human immunodeficiency virus (HIV).
5. Participants with any additional medical condition or illness that, in the opinion of the CI would interfere with study compliance and/or impair the participant's ability to participate or complete the study. Concurrent diseases or conditions that may interfere with study participation or safety include liver disease, bleeding disorders, arrhythmias, organ transplant, organ failure, current neoplasm, poorly controlled diabetes mellitus, poorly controlled hypertension, clinically significant haematological or biochemical abnormality.
6. Patients with a history of substance abuse (e.g. alcohol or drug abuse) within the previous 6 months before enrolment.
7. Participants with a history of severe allergies.
8. Female participants who are lactating or pregnant (positive pre-randomisation serum pregnancy test) or plan to become pregnant during the study.
9. Hypersensitivity to Nicobion (nicotinamide) or any of the excipients in this preparation
10. Liver function tests outside the normal range: aspartate aminotransferase (AST), alanine aminotransferase (ALT), bilirubin which in the opinion of the CI would put the participant's safety at risk.

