#### **4.9. Withdrawal of Participants from Study**

At any time, participants may withdraw from the study (i.e. withdraw consent to participate) at their own request and without giving reasons. Participation in the study may be discontinued at any time at the discretion of the CI and in accordance with their clinical judgment. No disadvantage will arise for any participant who withdraws consent for participation at any time or who is withdrawn from the study by the CI.

Reasons for discontinuation of study treatment will be recorded on the electronic Case Report Form (eCRF) in any case and may include the following:

- Participant's request for withdrawal
- CI's decision that discontinuation is in the best interest of the participant
- Non-compliance with the regimen and timing
- Development of an intolerable AE due to study participation as determined by the CI, participant or both
- Development of an intercurrent illness, condition, or procedural complication, which would interfere with the participant's continued participation
- Discovery that the participant entered the study in violation of the protocol or occurrence of a significant protocol violation during the study
- Data that becomes available that raises concern about the safety of the study drug so that continuation would pose potential risks to the participant
- Participant becomes pregnant
- Participant is lost to follow-up
- Any participant who discontinues treatment for medical reasons, e.g. because of AEs or clinical laboratory abnormalities, should be followed up at medically appropriate intervals in order to evaluate the course of the event and to ensure reversibility or stabilisation of the abnormality or event. The subsequent outcomes of these events will be recorded on the eCRF. However, if these events are attributable to deterioration of the disease, no such measures will be suggested.
- If a participant fails to return for a scheduled visit, a documented effort must be made to determine the reason. All attempted contact (telephone, emails or letters) must be filed in the participant's medical notes.

An Interventional End of Study (EOS) Visit will be done for each participant who completes the interventional study or who receives any study drug and withdraws prematurely from the study.

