| Chromatin study     | Chromatin will be extracted and stored at -80 C.
Spatial organisation of the FXN locus will be analysed by 3C-sequencing to correlate with FXN expression (Part IV).                                                                                                   |

Routine clinical laboratory parameters [haematology, chemistry, liver function tests (LFTs) etc] will be analysed by the local hospital laboratory (Hammersmith Hospital).

Blood glucose will be measured using a BM stick.

Pregnancy will be tested by serum for the interventional study and by urine for the non-interventional study.

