#### **7.8. Screening and Baseline**

Screening procedures (unless otherwise specified below) must be performed no more than 28 days prior to the first dose of study drug. Prior to performing any study-related assessments, the CI or delegates will inform the participant about the potential benefit and any risks associated with the participation in this trial. Participants and their GPs will be given an information sheet and given as much time as they wish to read and ask questions prior to giving informed consent.

After having given their informed consent, participants will undergo the following screening evaluations:

- General medical and drug history, including recording of demographic data; concomitant diseases; review of medication(s) or investigational products taken or investigational devices

- used in the past 30 days and medications taken for the treatment of FRDA in the 8 weeks prior to enrollment; and complaints/symptoms for baseline safety evaluation.
- Physical examination (including body weight and height) and evaluation of disabilities.
- Participants who will enter Part III and not Part II of the study will also be assessed using the FARS, SCAFI and speech dysarthria assessment.
- Blood samples will be taken for standard clinical laboratory tests (haematology, chemistry and LFTs), BM (measured by stick) and FXN level and baseline chromatin studies. Women of childbearing potential will also be tested for pregnancy.
- Urinalysis.
- Vital signs (BP, temperature and heart rate).
- ECG.

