### 8.4. Serious Adverse Event/Serious Adverse Drug Reaction

During clinical investigations, serious AEs (SAE) may occur. If the event is suspected to be drug-related, the event may be significant enough to lead to important changes in the way the medicinal product is developed (e.g. change in dose, population, needed monitoring, consent forms). This is particularly true for reactions, which, in their most severe forms, threaten life or function.

An SAE or serious adverse drug reaction (serious ADR) is any untoward medical occurrence that:

- Results in death.
- Is life-threatening. 'Life-threatening' refers to an event in which the participant is at risk of death at the time of the event; it does not refer to an event which hypothetically might have caused death if it were more severe (ICH E6).
- Requires in-participant hospitalisation or prolongation of existing hospitalisation.
- Results in persistent or significant disability/ incapacity (as per reporter's opinion).
- Is a congenital anomaly/birth defect.
- Is another medically important condition. Important medical conditions that may not result in death, be life-threatening or require hospitalisation may be considered as SAEs or SADR when, based upon appropriate medical judgment, they may jeopardize the participant or may require intervention to prevent one of the outcomes listed in the definition above. Examples of such events are intensive treatment in an emergency room or at home for allergic bronchospasm; blood dyscrasias or convulsions that do not result in hospitalisation; or development of drug dependency or drug abuse.
- Please note: Serious is not synonymous with severe. An event may be severe (e.g., severe headache) but still be of minor medical significance. Serious refers to an event that poses a threat to the participant's life or functioning.

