## **8.7. Adverse Event Recording and Reporting**

### **8.7.1. Adverse Event Recording**

All AEs will be recorded throughout the study from 1st IMP administration until the end of follow-up.

Each AE occurring to a participant, either spontaneously revealed by the participant or observed by the CI or delegates, whether believed by the CI or delegates to be related or unrelated to the study drug, must be recorded on the eCRF. Type and severity of AEs will be reported by the participants without being given a list of fixed symptoms beforehand.

The CI or delegates will also determine causality of any AE to the IMP and record it on the eCRF as well as their severity, time of onset, duration, and the precautions carried out, and whether or not the event meets one or more of the definitions of an SAE.

Laboratory results will be recorded on the eCRF and the CI or delegates will indicate whether abnormal results (high or low) are clinically or not clinically significant (CS or NCS). Clinically significant laboratory abnormalities, CS changes in vital signs (e.g., tachycardia) or other CS changes observed by the CI or delegates will be entered onto the eCRF.

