| Height                                                                                           | X                          |                                  |                    |                     |                     |                     |
| Weight                                                                                           | X                          |                                  |                    |                     |                     |                     |
| Urinalysis                                                                           | X                          |                                  |                    |                     |                     |                     |
| Haematology  , Chemistry, Electrolytes and LFTs incl blood glucose measured by stick | X                          | X*                               | X*                 | X*                  | X*                  | X*                  |
| Pregnancy test                                                                       | X                          |                                  |                    |                     |                     |                     |
| AE/ Con-meds                                                                                     | X                          | X                                | X                  | X                   | X                   | X                   |
| Vital Signs                                                                          | X                          | X                                | X                  | X                   | X                   | X                   |
| 12-lead ECG                                                                          | X                          |                                  |                    |                     |                     |                     |
| Chromatin studies                                                                                | X                          |                                  |                    |                     |                     | X**                 |

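### The dosing parts schedule one pregnancy test, at screening, although pregnancy is an exclusion and a listed reason for stopping nicotinamide, so nothing scheduled would reveal a pregnancy that begins during dosing

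*Protocol*

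**What the plan says.** **Entry.** Section 4.5 of the protocol excludes "Female participants who are lactating or pregnant (positive pre-randomisation serum pregnancy test) or plan to become pregnant during the study". Section 4.4 admits women of childbearing potential who agree to abstinence or to one of the listed contraceptive methods. Section 7.8 places the test among the screening evaluations: "Women of childbearing potential will also be tested for pregnancy". It allows screening procedures up to 28 days before the first dose.

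**Type of test.** Section 7.5 fixes the sample but no frequency: "Pregnancy will be tested by serum for the interventional study and by urine for the non-interventional study".

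**Schedule.** In section 12.1 the pregnancy row is ticked at screening. It is empty for Part I visits 1 to 5, Part II days 1 to 5, Part III weeks 1 to 8 and the end-of-study visit. The visit procedures in sections 7.9, 7.10 and 7.11 list safety bloods, vital signs, adverse events and frataxin samples, but no pregnancy test.

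**Discontinuation.** Section 4.9 says that reasons for discontinuing treatment are recorded and may include "Participant becomes pregnant".

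**Safety reporting.** Section 8.4 lists among the criteria for a serious adverse event: "Is a congenital anomaly/birth defect". Section 8.7.1 limits adverse-event recording to the period from the first "IMP administration until the end of follow-up". Sections 7.11 and 12.1 put the end-of-study visit 1 to 8 weeks after the last dosing part.

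**The concern.** The protocol treats pregnancy as incompatible with dosing at entry and as a reason to stop afterwards, but its schedule looks for pregnancy only at entry. Nothing scheduled before Part II, before the Part III supply is released or during Part III would show that a woman had conceived since screening. Section 8 describes the trial as the first use of nicotinamide in people with Friedreich's ataxia. The single doses in Part I go up to 8 g, and dosing is then daily in Parts II and III.

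Two things are at stake. The first is participant protection: a woman could pass from Part I into two months of daily dosing on the strength of one early test. The second is the meaning of the safety report: a statement that no pregnancies occurred would carry little information if none were looked for on a schedule.

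The congenital-anomaly criterion has a related difficulty, because the recording window closes soon after dosing ends.

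**Working it through.** No sample size, power or significance level is involved. The check is a count of scheduled tests and some day arithmetic.

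**1. Scheduled tests (section 12.1, checked against 7.8 to 7.11)**

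| Period | Visits or days | Pregnancy tests |
|---|---|---|
| Screening | 1 | 1 |
| Part I | 5 | 0 |
| Part II | 5 | 0 |
| Part III | 8 | 0 |
| End of study | 1 | 0 |

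After screening: 5 + 5 + 8 + 1 = 19 visits or days, with 0 tests. The table and the visit text agree, so the blanks are not a fault in how the table was read.

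**2. Interval from the test to the end of Part III, for a participant in Parts I to III**

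Inputs: screening at most 28 days before Day 1; Part II day 5 no earlier than Day 39; Part III of 8 weekly visits, each 7 ± 2 days.

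- End of Part III at nominal spacing: 39 + 8 × 7 = 39 + 56 = Day 95.
- Test on Day 1: 95 − 1 = 94 days.
- Test 28 days before Day 1: 94 + 28 = **122 days**.
- Every Part III interval at +2 days: 39 + 8 × 9 = 39 + 72 = Day 111, so 111 − 1 + 28 = 138 days.

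None of these is an upper bound. The Part I and II days in 12.1 are minimums, and section 4.1 allows time off drug for safety reasons to be added to the end of Part III.

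**3. Participants who enter Part III directly**

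28 + 56 = 84 days, or 28 + 72 = 100 days with the +2-day windows.

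**4. Recording window**

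The end-of-study visit adds 1 to 8 weeks, that is 7 to 56 days, again with no test. From the screening test to the close of recording is therefore at most 122 + 56 = 178 days at nominal spacing, or 138 + 56 = 194 days with the wide Part III windows, both at the shortest Part I and II spacing. Either is shorter than a full-term pregnancy (general knowledge, not a figure in the protocol). At that spacing, an anomaly first recognised at term birth after a conception later than screening would appear after routine recording had ended. Sections 8.7.2 and 8.7.3 continue follow-up beyond the reporting period, but only for a serious adverse event already reported. Section 8 contains no provision to report a pregnancy or follow it to its outcome.

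**5. Timing reference for the single test**

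Section 4.5 ties the test to a point before randomisation, but no randomisation is described. Part I follows the fixed schema in Table 1 of section 4.1, and allocation to no drug in Part II is at the chief investigator's discretion.

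**The case against.** The strongest reply is that there is no outright contradiction. Sections 4.5, 7.8 and 12.1 consistently describe an entry test, and nothing promises repeat testing. Contraception is a condition of entry, and women planning pregnancy are excluded. The reference safety table in section 8.1 lists no reproductive hazard. Section 4.9 gives reasons that may be recorded, not a stopping rule driven by a test. Adverse events and medications are reviewed at every visit, participants are reviewed before discharge, and Part III has a diary. Much of the interval in Part I is washout between single doses at least a week apart.

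Most of this is fair and limits the point. Contraception lowers the risk but detects nothing, and the reviews and diary depend on the participant knowing that she is pregnant. Re-screening before Part III is discretionary and concerns only those who took part in Part I but not Part II.

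Three stronger readings are tempting, and the protocol supports none of them:

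- **That the pregnancy criterion cannot operate.** It can, through self-report, an unscheduled test or re-screening. What is missing is a scheduled means of finding the event.
- **That Part IV, without drug, sets a testing standard which the dosing parts drop.** Part IV does repeat the test at its four time points, but for imaging safety: "Urine pregnancy test only for women of child-bearing potential (prior to fMRI"). It is not a standard for drug exposure, so a comparison of test counts proves nothing.
- **That an anomaly could never be captured.** One recognised and reported before the end of follow-up would be recorded and followed. The gap concerns those that appear later.

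**Conclusion.** The point stands as a gap in ascertainment and as a patient-safety matter that should be closed. After one test at screening there are no scheduled tests at 19 visits or days, while pregnancy remains a listed reason for discontinuing treatment.

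The size is up to 122 days from the test to the end of Part III. This assumes participation in Parts I to III, screening at the 28-day limit, the shortest Part I and II spacing and nominal weekly Part III visits. It is the time without a scheduled test, not the time on daily drug. It is shorter for direct entrants to Part III and longer when visits spread out.

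The mismatch between the congenital-anomaly criterion and the recording window is a second, smaller gap. The reference to randomisation in section 4.5 is a separate wording error, but it leaves the timing of the only test without a defined anchor.

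**What to change.** Reconcile sections 4.5, 4.9, 7.5, 7.8, 8.4 and 8.7.1 with schedule 12.1 on two matters:

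1. The pregnancy discontinuation reason should have a scheduled means of ascertainment during the dosing parts. Existing visits and samples can be used. Which visits, and what follows from a result, are for the sponsor to decide; no testing calendar or clinical rule is proposed here.
2. The recording window should be consistent with counting a congenital anomaly as a serious adverse event. The protocol should say how such an outcome would reach the safety data if it appears after the end-of-study visit.

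In section 4.5, replace the reference to randomisation with a time point that exists in this design.

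The cost is a few add-on tests per woman of childbearing potential and some protocol wording. Blood is already drawn for clinical chemistry and haematology at the Part I to III visits and at the end of study (section 7.6), so no extra visits are needed.
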